## Objectives {7}

The primary objective of this study is to assess the effect of EMDR treatment on abdominal pain in IBS. It is hypothesized that participants in the EMDR treatment condition will show a greater reduction in abdominal pain intensity than those in the wait-list control group.

Our secondary objectives are to determine the effects of EMDR treatment on (1) other salient IBS symptoms (personalized), (2) overall severity of IBS-related symptoms, (3) the hindrance of valued activities caused by abdominal pain (personalized), (4) quality of life, and (5) the reported rate of adequate relief from IBS symptoms.

It is hypothesized that EMDR treatment will, as compared to the wait-list control condition, lead to a significantly greater reduction of salient symptoms, the overall severity of IBS symptoms, and the experienced hindrance of valued activities. Furthermore, we hypothesize that quality of life will show greater improvement in the treatment condition (EMDR) than in the wait-list control condition, and that after treatment and at follow-up, a higher percentage of patients in the treatment condition (EMDR) will indicate experiencing “adequate relief” of IBS symptoms than in the wait-list control condition.

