### Outcomes {12}

The primary outcome of this study is the intensity of abdominal pain. As the intensity of abdominal pain in IBS can vary greatly from day to day, we have chosen to pose the same question each day for 2 weeks. Participants answer the question: “How much did you suffer from abdominal pain during the last 24 h?”. The subject’s answer is given on a 21-point Likert scale (0 = no pain, 10 = worst pain imaginable, half points possible).

In addition to the primary outcome measure (abdominal pain), we pose four other diary questions at the same time, during the same period, with the same 21-point Likert scale. Based on their statements at inclusion about their principal IBS symptoms, we ask about their top two symptoms (abdominal pain excluded): “How much did you suffer from (complaint) during the last 24 h?” (0 = not at all, 10 = extreme suffering, half points are possible). These symptoms could be frequently occurring IBS symptoms such as diarrhea, constipation, and bloating, but they can also be more idiosyncratic such as dizziness. We also ask about the hindrance subjects have experienced from their IBS symptoms when engaging in everyday activities. Based on their statements at inclusion about the two- valued activities that are most impeded by the IBS symptoms, we ask for every one of these activities: “How much hindrance have you experienced from your IBS symptoms when engaging in this activity?” (0 = no hindrance at all, 10 = made completely impossible; half points possible). Activities most likely to be impeded by IBS symptoms are working, doing sports, going out for dinner, and going out (dancing, theatre, etc.).

The 14-day-sequence of these 5 “diary questions” is administered at inclusion, 8 weeks after inclusion (for the intervention condition this means after treatment), and at follow-up (20 weeks after inclusion, 3 months after treatment).

In addition to the diary questions, we administer several questionnaires, the purpose of which is to describe the population and to either confirm or disconfirm the results of the diary questions. They also enable comparing outcomes with those of other studies. The questionnaires are administered on the last day of every 14-day-sequence of diary questions.

The questionnaires administered are:IBS-SSS (Irritable Bowel Syndrome—Severity Scoring System) [35].

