### Sample size {14}

Several factors have influenced the sample size in this study: setting, method of analysis, and the estimate of comparability with previous scientific research.

As the study is conducted as part of the curriculum of a training course taken by the principal investigator, both time and resources are limited. Our aim is to demonstrate a clinically relevant treatment effect regarding the primary outcome measure with a limited sample size.

The design of our study enables us to analyze our primary outcome data (pain score diary) using a linear mixed effects models analysis. Sample size was computed using the online statistical calculation program GLIMMPSE (General Linear Mixed Model Power and Sample Size): https://glimmpse.samplesizeshop.org/#/ using an alpha of 0.05 and a desired minimum power of 0.80.

The most important estimated value required by the GLIMMPSE program is the expected effect size. Since a study on the effect of EMDR on abdominal pain in IBS has never been done before, a search was made for comparable research. A review on EMDR treatment for chronic pain found large effect sizes [22]. The EMDR for phantom limb pain study design is most comparable to our study design [28]. Based on this study, a remarkably large effect size d of 1.22 was calculated. On entering this effect size, GLIMMPSE calculated that a sample size of 12 should be sufficient. However, when a demonstration of an average effect size is wanted, a sample size of 24 is needed. This sample size is adequate to analyze the primary outcome measure daily pain scores using a linear mixed effects model. In addition, this sample size is also expected to be adequate to analyze the secondary outcome measures from the standardized questionnaires (measures taken only three times in total) with LME models. Taking drop-out into account we decided to include a maximum of 34 participants.

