## Statistical methods

### Statistical methods for primary and secondary outcomes {20a}

The statistical analyses will be performed according to the intention-to-treat principle.

The primary outcome measure in this study is the reported intensity of abdominal pain, which is registered during 14-day periods of daily diary questions, at three points in time, yielding 42 data points per participant.

The principal research question will be answered by performing a linear mixed effect models analysis, based on 2 groups (treatment and control) and 3 (baseline, after treatment, follow-up) × 14 (days) measuring moments. Before the analysis, data will be checked for outliers and the assumption of linear relations. Values with an absolute *z*-score > 4 will be treated as outliers and removed.

The model will be built in a stepwise model, first fitting an intercept-only linear mixed effects model, allowing to disentangle variance between patients and variance within patients over time. In a second step, the predictor time will be added, to control for any unexplained changes over time in subsequent models. If necessary, a quadratic term for time will be added to the model as well. Subsequently, in the third model, the fixed effect for condition will be added. In the fourth model, the fixed effect for measurement period (baseline, treatment, and follow-up) will be added (note, this variable will represent the difference between baseline and treatment period and baseline and follow-up period irrespective of condition). In the sixth model, the difference between measurement periods will be allowed to vary over patients (a so-called random slope for measurement period). If this is significant, in a seventh model, an interaction between measurement period and condition will be included, to explain why the differences between periods vary over patients. This last term, the interaction between measurement period and condition, answers our primary research question: what is the overall difference in changes in pain score over measurement periods between condition and control group?

After performing the analysis, the assumption of normally distributed errors for both level 1 and level 2 errors will be assessed.

As to the secondary outcome measures: the data gathered from the residual diary questions (pertaining to other IBS symptoms and hindrances experienced in valued activities) are analyzed in the same way as the primary outcome (abdominal pain intensity).

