The outcome measures from the two standardized questionnaires, which only yield 3 data points, will be analyzed by LME models based on 2 groups (treatment and control) and 3 measuring moments (at baseline, after treatment, and at follow-up). See Fig. 2.

For all analyses regarding symptom improvement, a one-sided significance threshold of alpha = 0.05 will be used. For all other analyses, a two-sided* p* value of 0.05 will be used as the significance threshold. We will report both *p*-values and 95% confidence intervals.

Based on the Adequate Relief Question, and based on the presence of a clinically relevant reduction of symptoms as measured by the IBS-SSS, a Number Needed to treat will be calculated, for two measuring moments: after treatment and at follow-up.

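### The period × condition term that answers the primary question is fitted only if the random slope for period is significant, and no primary result is stated if it is not

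*Protocol article*

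**What the plan says.** The hypothesis under Objectives {7} concerns means: "participants in the EMDR treatment condition will show a greater reduction in abdominal pain intensity than those in the wait-list control group".

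The section on statistical methods for primary and secondary outcomes {20a} describes a sequence of models for the diary pain score. After time, condition and measurement period have been added as fixed effects, it continues: "In the sixth model, the difference between measurement periods will be allowed to vary over patients (a so-called random slope for measurement period"). The next sentence sets a condition: "If this is significant, in a seventh model, an interaction between measurement period and condition will be included". The purpose it gives for the interaction is to account for variation between patients in their period differences. It then says: "This last term, the interaction between measurement period and condition, answers our primary research question".

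The remaining diary questions (other symptoms, hindrance of activities) are to be analysed in the same way. The article does not say that the interaction is fitted regardless, and it gives no primary result for the case where the slope is not significant.

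**The concern.** A variance test decides whether the primary test takes place, and the two address different questions. The slope test asks whether patients differ in how much they change. The hypothesis asks whether the arms differ in mean change. The second can be true without the first being detectable.

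If the slope test fails, none of the earlier models can stand in. The condition effect in the third model averages over all periods, baseline included. The period effect in the fourth is, by the article's own note, taken irrespective of condition. Read literally, the trial could then end without an estimate, p-value or confidence interval for its primary question, whether or not EMDR works. The power target under Sample size {14} ("using an alpha of 0.05 and a desired minimum power of 0.80") is not described as allowing for a two-step procedure.

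**Working it through.** **The plan's own figures.** The sample sizes of 12 and 24 cannot be recomputed, because the variances, correlations and the size of the average effect entered into the power program are not given. The point does not depend on them.

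**Inputs from the article.** 24 patients needed and at most 34 included, 1:1; 3 periods × 14 days ("yielding 42 data points per participant"); a 0–10 scale ("0 = no pain, 10 = worst pain imaginable, half points possible"); for symptom improvement, "a one-sided significance threshold of alpha = 0.05 will be used".

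**Assumed, not in the article.** Daily SD 1.8 points; benefit δ at both later periods; slope SD = SD of patients' own deviations in period change, drawn independently for the two later periods. A deviation shared by both periods gives the slope test less to detect and would lose somewhat more. The between-patient SD (1.3) cancels from change scores. The article does not say how slope significance is judged, so an F test of patient × period and a 5-df likelihood-ratio test were both tried.

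**Step 1: the primary contrast without the condition** (post-treatment minus baseline, N = 24, δ = 1.0, slope SD 0).
- Variance of a patient's change in 14-day means: 2 × 1.8²/14 = 0.463.
- SE of the difference between arms: √(0.463 × 4/24) = 0.278.
- Non-centrality: 1.0/0.278 = 3.60 on 22 df, giving one-sided power of about 0.97.

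**Step 2: the slope test in the same setting.** The sixth model has no interaction, so a uniform benefit in half the patients appears as slope variance of about δ²/4 = 0.25.
- Degrees of freedom: (24−1)(3−1) = 46 and 24 × 3 × 13 = 936.
- Patient × period sum of squares: 24 × ¼ × δ² × (4/9 + 1/9 + 1/9) = 4δ².
- Non-centrality: 14 × 4/1.8² = 17.3. The slope test passes in about 0.47 of trials.

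The same signal gives the slope test a pass rate of 0.47 and the primary contrast a power of 0.97. The probability of clearing both is about 0.46.

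**Step 3: relaxing the assumptions** (simulation, N = 24, F test, one-sided 0.05).

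| Benefit | Slope SD | Day-to-day autocorrelation | Power, always tested | Power, as written |
|---|---|---|---|---|
| 1.0 | 0 | 0 | 0.97 | 0.46 |
| 1.0 | 0.3 | 0 | 0.94 | 0.74 |
| 1.0 | 0.5 | 0 | 0.87 | 0.84 |
| 1.0 | 0 | 0.3 | 0.84 | 0.83 |
| 1.0 | 0.5 | 0.3 | 0.73 | 0.73 |
| 1.7 | 0 | 0 | 1.00 | 0.98 |

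At slope SD 1.0 there is no loss. The 1.7-point row corresponds to the only numerical effect size in the article, d = 1.22, on the assumed SD of a 14-day mean: 1.22 × √(1.3² + 1.8²/14) = 1.22 × 1.39 ≈ 1.7.

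**Step 4: the likelihood-ratio version** (two-sided, 300 trials per setting, error about ±3 points).
- Uniform benefit, independent days, N = 24: 0.95 falls to 0.24 (F test: 0.49). N = 34: 0.98 falls to 0.31 (F test: 0.60).
- Slope SD 0.5, N = 24: 0.81 falls to 0.63 (F test: 0.80).
- Autocorrelation 0.3, N = 24: 0.78 falls to 0.72 (F test: 0.78).

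**Step 5: dependence on daily noise** (N = 24, uniform 1.0-point benefit, independent days). The slope test passes (F / likelihood ratio) in 68% / 39% of trials at daily SD 1.5, 37% / 12% at SD 2.0 and 20% / 5% at SD 2.5.

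**The case against.** The large losses need three things together: a modest effect, almost no variation between patients in their change, and independent diary days. The article points the other way. It describes symptoms that vary over time, a considerable placebo response, and treatment targets chosen per patient. With slope SD 0.5 and autocorrelation 0.3 together, power is 0.73 with or without the condition. Nor is a uniform benefit invisible to the slope test, since it contributes δ²/4 to the slope variance, and an effect of the size cited from the phantom-limb study would nearly always pass. All of this stands, and it rules out presenting the fall from 0.97 to 0.46 as the expected result.

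A reader might also infer an inflated false-positive rate, because the random slope seems to be kept or dropped on significance and an interaction tested without it would have too small a standard error. The text does not support this. When the slope is not significant, the interaction is not fitted at all, so an interaction test without the slope never arises.

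It might also be said that an analyst would fit the interaction anyway, or that a separate analysis plan settles it. But the article has not left a detail open here. It states a decision rule, and nothing in it lifts that rule. The objection limits the size of the harm and does not remove the defect.

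**Conclusion.** The concern holds as a fault of logic and prespecification. The only analysis that answers the primary question is conditional on a variance test that does not address the hypothesis, no result is defined if that test fails, and the other diary outcomes share the rule.

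The cost in power is a range resting on assumed variances. With 24 patients, a 1.0-point benefit and the F test, it runs from about half the power (0.97 to 0.46) for a uniform benefit with independent days, through 0.94 to 0.74 at slope SD 0.3, to little or nothing at slope SD 0.5 or more, with autocorrelation of 0.3, or with an effect near 1.7 points. A likelihood-ratio test loses more. The exposure is greatest for moderate effects, and the article chose 24 rather than 12 in order to detect an average effect, whose size it does not state.

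These figures do not show that the trial is likely to miss a real effect, nor that the stated sample size is wrong.

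**What to change.** In {20a}:

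- Remove the significance of the random slope as a condition for fitting the interaction.
- Name one confirmatory model for pain and for every other diary outcome: fixed effects for measurement period, condition and period × condition, with the planned time terms; a random intercept and random period effects per patient, always retained.
- State that the interaction is tested and reported, with its estimate and confidence interval, whatever the random-slope test shows.
- Keep the earlier models in the sequence as a description of the variance only.

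Small-sample degrees of freedom (Kenward-Roger or Satterthwaite) would be a sensible addition but are optional.

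The cost is a change of wording, made before the data are analysed. It needs no further patients, measurements or visits.

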### Interim analyses {21b}

No interim analyses or other stopping guidelines will be applied.

### Methods for additional analyses (e.g., subgroup analyses) {20b}

If the collected sample size allows it, it will be investigated whether observed differences between patients in treatment effect can be explained by other variables such as sex, age, symptom severity at baseline, the severity of PTSD-related symptoms at baseline, and the number of other ongoing treatments (such as diets, etc.).

In describing the study population, the following data will be reported:The frequency of reported IBS symptoms and valued activities (as reported at initial screening).The percentage of patients that meet the criteria for PTSD (as determined by LEC-5 and PCL-5 results).Average and standard deviation scores on PCL-5, per group and per measuring moment.The number of patients that have experienced additional traumatic experiences during the time of participation.

Chi-square tests or *t*-tests will be done to test for a priori differences between the intervention and control group regarding demographic and descriptive values. Both *p* values and standardized differences will be reported.

### Methods in analysis to handle protocol non-adherence and any statistical methods to handle missing data {20c}

Every effort is made to avoid missing data. The way the diary questions and questionnaires are administered online makes it impossible to skip a question. Also, patients who do not complete a questionnaire or diary will receive one or more reminders.

For all analyses, a linear mixed effects model (LMEm) analysis is used. The advantage of linear mixed effects modeling is that the analysis can be performed on all data available, and missing data is handled automatically assuming Missing at Random (MAR) without requiring imputations.

### Plans to give access to the full protocol, participant-level data, and statistical code {31c}

Statistical code will be made available through a publication via https://zenodo.org/.

See {31a} for further information.

## Oversight and monitoring

### Composition of the coordinating center and trial steering committee {5d}

As this is a small mono-center study. The study board which acts as a steering committee consists of only two people, the principal investigator and the primary EMDR consultant. The study board meets every month and reviews the progress of the study. Final decisions on changes to the protocol, publications, and reporting will be made by the study board.

The principal investigator keeps in regular contact with the gastroenterologists, research assistant, and trial therapists and provides them with day-to-day support.

This study will not be audited by independent auditors. There is also no data monitoring committee as the study involves minimal risk. The intervention (EMDR) is part of regular care.

### Composition of the data monitoring committee, its role and reporting structure {21a}

See {5d}.

### Adverse event reporting and harms {22}

The research protocol, including plans for managing adverse events, has been reviewed and approved by the human ethics and research committee MEC-U (reference number: NL71740.100.20).

As is usual when applying psychological interventions, patients may temporarily experience mild reactions such as fatigue and heightened emotionality, which is seen as the result of the ongoing effect of the intervention.

Any serious adverse effects (SAEs) as defined by the Central Committee on Research Involving Human Subjects (CCMO in Dutch) will be documented and reported immediately to the principal investigator. It will be determined whether the SAE is related to any trial procedure or intervention.

### Frequency and plans for auditing trial conduct {23}

The study will not be audited by independent auditors. To this, the human ethics and research committee MEC-U has given its assent.

### Plans for communicating important protocol amendments to relevant parties (e.g., trial participants, ethical committees) {25}

Any protocol modifications which may affect the conduct of the study or patient safety require formal amendments to the protocol. These will be agreed to by the study board and must be approved by the MEC-U ethics committee and the institutional review board prior to implementation. The results of amendments will be communicated to trial participants if relevant.

Minor changes to the protocol (e.g., corrections, clarifications that have no effect on the way the study is conducted) will be agreed upon by the study board.

## Dissemination plans {31a}

After completion of the study, the results will be submitted for publication to a peer-reviewed scientific journal, regardless of the direction or magnitude of effects. Also, we intend to present the results at relevant research conferences, and in (inter)national publications. And finally, if results warrant it, they will be used for educational and training purposes.

The institutions providing grants will not impose restrictions on publication.

Participants will receive the final trial report on request, as well as any other parties who have shown an interest (such as the participants’ general practitioners). Also, participants will be offered an overview of their own results on several outcome measures.

The research protocol, data, and statistical code supporting the findings of the final trial report will be available on request, if deemed reasonable and in accordance with the EU general data protection regulation.

The investigators involved and the statistician engaged for the analysis will be named as (co-) authors of the publication of the final trial report.

## Discussion

This article described the study protocol of a hospital-based RCT on EMDR and wait-list control in IBS patients. The primary aim of the study is to gain insight into the effect of EMDR treatment on abdominal pain in patients with IBS. As IBS is a highly prevalent condition, and there are very few effective and acceptable treatment options for IBS in general, and for IBS-related abdominal pain specifically, this study could have important implications for clinical practice. If we find that EMDR is indeed effective in reducing abdominal pain in IBS, this study may contribute to important advances in the psychological treatment of patients with IBS and thereby might have considerable positive impact on both the individual lives of IBS sufferers and the societal burden that IBS causes.

This study has several strengths. First, to our knowledge, this study will be the first to investigate the effectiveness of EMDR on abdominal pain in IBS in a randomized controlled trial. The association between PTSD and IBS has been well established in various populations [43] and suggestions have been made to expand research into the effect of psychological treatments on IBS symptoms [44]. Two case studies have been published that show that trauma-focused treatment can alleviate IBS symptoms [45, 46], but more systematical and empirical studies are lacking.

Second, we have chosen our various outcome measures to optimize information yield. In the population of IBS sufferers, symptoms tend to vary over time and main symptoms differ per person [9, 20]. To address this problem, we chose to (1) gather data points over an extended period of time (i.e., 2 weeks at baseline, after treatment, and at follow-up) and (2) personalize secondary outcome measures. This provides us with an accurate representation of symptoms and does justice to what is important to the participant. However, to enable comparison to other studies in the IBS realm, several standardized questionnaires are administered that are widely used and recommended [47] in IBS research: the IBS-Severity Scoring System, the IBS-Quality of Life measure, and the IBS-Adequate Relief question. From the IBS-SSS, two measures can be gleaned: (1) the numeric overall score and (2) a dichotomic score of clinically significant improvement of symptoms (50 points reduction of the overall score is considered to represent a clinically relevant improvement) [35].

Third, inclusion in the study will be shortly after being seen by the gastroenterologist. This assures that participants are representative of the patient population referred to secondary care. As the population and conditions reflect clinical practice, generalizability of the results of the study to routine clinical practice is enhanced. Lastly, treatment integrity is ensured by intensive supervision by experts and regular fidelity checks.

There are also some limitations to this study that should be considered. First, our wait-list control condition does not allow us to rule out a positive effect of “therapist contact” on participants’ abdominal pain. Designing an adequate control intervention in research on the effectiveness of psychological treatments is difficult [36, 48]. A proper placebo condition has all components of the experimental treatment, except the actual operating mechanism of this treatment. In psychotherapeutic interventions, all non-specific components of treatment such as time, attention, and contact with therapist should be integrated into the control condition [49]. Moreover, a control intervention which the participants would not consider credible can have a negative impact on the study results and participant motivation causing dropout [48].

Alternatively, comparing EMDR to an active control group, such as gut-directed hypnotherapy or psychoeducation would supply information on the relative efficacy of these treatments.

Due to restrictions in time and resources, we are forced to choose a design that allows us to keep within feasible limits. A proper placebo condition would require more time and resources than we have available. The same applies to the comparison to an active control condition, which would require a larger sample size.

Second, we cannot adjust optimally for a placebo effect. The placebo response in RCTs in IBS is estimated to be considerable [50, 51]. Several recommendations have been made to diminish the effect of placebo response on outcomes of RCTs [49, 52, 53]. We have managed to follow (or nearly follow) the recommendations as to the length of follow-up, the duration of treatment, and using stringent inclusion criteria, but blinding to treatment is impossible, and we have not distinguished between subgroups of IBS (predominant constipation, diarrhea or mixed), or included biomarkers as outcome measures.

Third, it is likely that our sample reflects a selection bias based on the acceptability of the intervention. Medical treatments such as tablets or diet were found to be easily acceptable to most IBS patients, but psychological intervention may not be as readily acceptable to everyone [54]. Both acceptability and credibility of psychological treatment for Persistent Physical Symptoms (formerly Medically Unexplained Symptoms, MUS) are found to be important for successful implementation [55]. It has been suggested that it is crucial that doctors communicate to their patients that attention to psychosocial factors does not preclude vigilance to physical disease. This reduces anxiety about missing a medical problem and enhances the patients’ willingness to accept a biopsychosocial explanation for their symptoms [56]. It may very well enhance the acceptability of psychological treatment as well. In further research, the addition of this assurance by the gastroenterologist may decrease selection bias.

In conclusion, the results of this randomized controlled trial, evaluating the effectiveness of EMDR treatment on abdominal pain in IBS, will contribute to the advancement of IBS management.

